#### Sensitivity analysis population

2.5.1

A pre-specified sensitivity analysis will additionally include women experiencing early neonatal death within 24 h of live birth in the study blocks during the same period.

The physiology of postpartum recovery is identical to that following stillbirth, and existing evidence demonstrates overlapping grief and depressive symptom profiles during the first six postpartum weeks (25, 26). However, as C-COMPASS was co-designed around the stillbirth experience-where the mother has not held a living infant-the counselling narrative requires sensitivity adaptation for women who briefly held a live-born baby.

Accordingly, early neonatal deaths will be enrolled separately with a subgroup identifier, excluded from the primary analysis, and included only in the pre-specified sensitivity analysis.

#### Target population

2.5.2

The intervention delivery comprises frontline community health workers, including Accredited Social Health Activists (ASHAs), Auxiliary Nurse Midwives (ANMs), and Community Health Officers (CHOs).

ASHAs serve as the primary implementers of the C-COMPASS intervention at the community level, delivering structured counselling during postnatal home visits. ANMs and CHOs provide supervisory and referral support, including initial clinical assessment and coordination of care. Where indicated, women identified with clinical or psychological complications are referred to higher-level providers, including obstetricians/gynaecologists and district-level mental health specialists (e.g., psychiatrists), as part of the established referral pathway.

### The C-COMPASS protocol

2.6

C-COMPASS is a structured, phased, community-based continuum of care co-designed through iterative consultation cycles within the SHRiSTI project. The co-design process involved district psychiatrists, programme managers and other district health authorities, ASHA workers, ANMs, CHOs, the district ASHA coordinator, specialist like obstetricians, implementation science experts, and national stakeholders engaged in stillbirth surveillance and guidelines. Additionally, insights were also obtained from the bereaved women through social autopsy.

The intervention is grounded in three core principles:
grief after stillbirth is a normal human response that requires acknowledgement rather than medicalisation;structured support must begin early, given the acute psychosocial vulnerability in the first 72 h after returning home; andthe ASHA-community relationship, built on geographic proximity and trust, provides the most appropriate platform for delivering community-based support.In addition, the intervention adopts an integrated approach that combines emotional support with basic physical health assessment and a structured referral pathway for identified red-flag conditions, ensuring continuity of care across community and facility levels.

The intervention architecture is designed to be adaptable to early neonatal death without requiring fundamental redesign.

#### Intervention deliverers

2.6.1

The intervention will be delivered by Accredited Social Health Activists (ASHAs), with support from the study team supervisors. ASHAs were selected as the primary implementers as they are trained under the National Health Mission (NHM) and function as the first point of contact between communities and the formal health system.

ASHAs are already mandated to conduct postnatal home visits under the Home-Based Newborn Care (HBNC) programme. C-COMPASS does not require the introduction of a new cadre of workers or additional visits beyond the existing postnatal care schedule. Instead, it integrates a structured counselling protocol, targeted training, and a defined referral pathway into routine ASHA-led visits. This design enhances feasibility and scalability by leveraging existing health system infrastructure and enables assessment of whether structured psychosocial support following perinatal loss can be delivered within the current system at marginal additional cost.

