##### Secondary

2.3.1.2

To assess the effect on functional impairment among women with stillbirths at Day 60 postpartum.To assess the effect on grief distress among women with stillbirths at Day 60 postpartum.To estimate the proportion of women screening positive for probable depression (EPDS ≥13) in each arm, as exploratory evidence for future trial designTo explore whether effects remain consistent when early neonatal deaths (<24 h) are included alongside stillbirth.To assess the feasibility of C-COMPASS delivery within the existing ASHA system, measured by 72 h ASHA visit coverageTo estimate the incremental cost of C-COMPASS per woman counselled compared to routine care.

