### Incremental cost analysis

2.9

An incremental cost analysis will be conducted from the health system perspective to estimate the additional cost of delivering C-COMPASS per woman counselled, compared to routine postnatal care. A full cost-effectiveness analysis will not be undertaken at this stage, as reliable effectiveness estimates and utility-based outcomes (e.g., QALYs or DALYs) are not yet available. The analysis is intended to inform programmatic decision-making by estimating the additional resources required for implementation.

Three cost components will be included.
First, ASHA time costs per case will be estimated based on self-reported time spent on each contact (72 h visit, Day 7 telephone call, Day 14 visit, and Day 42 visit), multiplied by an imputed hourly rate derived from the average monthly ASHA incentive.Second, direct ASHA costs will include out-of-pocket expenditures such as transport and printed materials incurred during service delivery.Third, programme-level costs will include ASHA training costs (trainer time and ASHA participation time, amortised over three years and allocated per expected annual caseload), CHO supervision time, nurse/ANM time for activities and any additional printing or documentation costs.The primary cost metric will be the incremental cost per woman counselled (INR). Secondary cost indicators will include cost per woman screened positive for depression and cost per referral completed. Cost data will be collected using a structured costing tool administered to ASHAs and CHOs at the end of the study period. Routine care costs in control blocks will be estimated to provide comparative context. All costs will be reported in 2026 Indian Rupees (INR), and no discounting will be applied given the short study duration. Findings will be interpreted in relation to existing benchmarks for community-based mental health interventions in low- and middle-income settings to support policy relevance.

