The implementation case for C-COMPASS rests on a single core argument: it is designed to be absorbed into the existing system, not added onto it. India's 1.04 million ASHAs are already mandated to conduct postnatal home visits under the Home-Based Newborn Care (HBNC) programme (10). C-COMPASS converts the visit that ASHAs already make after a stillbirth, currently an unstructured, informal, and inconsistent interaction, into a structured, documented, and evaluated care episode. The marginal resource requirement is a half-day training, a Hindi job aid, and a column in the existing ASHA register. The Tele-MANAS referral pathway ([name]) is already operational national infrastructure. The incremental cost analysis embedded in this study will quantify this argument in INR per woman counselled, the metric that government decision-makers require before considering programme adoption. The incremental cost analysis will determine whether C-COMPASS falls within the ₹200–500 per beneficiary threshold typical of scalable LMIC community health programmes. If C-COMPASS achieves the feasibility threshold of ≥70% 72 h visit coverage across both intervention blocks, it will demonstrate that ASHAs with targeted training can reliably identify and reach bereaved women in the critical early postpartum window, a finding that has direct programme planning implications at state and national level.

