
### Strengths and limitation

3.1

The study has several methodological and contextual strengths. First, the use of validated, multi-domain outcome measures, EPDS for depressive symptoms, SDS for functional impairment, and BGQ for complicated grief risk, provides a comprehensive and clinically meaningful picture of recovery at 60 days, going beyond single-domain assessments used in most comparable studies. Second, the separation of outcome assessment from intervention delivery, with independent study nurses administering all scales at Day 60 after the ASHA's Day 42 contact, minimises ascertainment bias and response priming, a methodological safeguard rarely implemented in community-based LMIC trials. Third, the four-block DiD design with block-level fixed effects provides a more rigorous quasi-experimental estimate than a single-site comparison, controlling for time-invariant block-specific confounders and enabling a more robust parallel trends assessment. Fourth, the sample size is grounded in empirical SHRiSTI ASHA surveillance data from 895 ASHAs across all Palwal blocks rather than published estimates or assumptions, producing a more realistic and defensible enrolment projection. Fifth, the systematic framework selection process, guided by the SELECT-IT meta-framework, ensures that each theoretical tool, TDF for barriers and facilitators, ERIC for strategy specification, Proctor for evaluation, is chosen against explicit criteria of purpose, attributes, and project fit, rather than by convention. Finally, embedding the study within a functioning implementation research programme ensures that implementation metrics reflect genuine health system performance rather than research-assisted delivery, which is essential for generating evidence that is usable by government programme managers.

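### Study-team support for delivery conflicts with the claim that the implementation metrics are not research-assisted, and that support is not costed

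*Protocol article*

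**What the plan says.** Section 2.6.1 (Intervention deliverers) defines who delivers C-COMPASS: "The intervention will be delivered by Accredited Social Health Activists (ASHAs), with support from the study team supervisors". It does not say what this support consists of.

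Other sections place supervision with the health system. Section 2.5.2 says "ANMs and CHOs provide supervisory and referral support, including initial clinical assessment and coordination of care". The Introduction locates supervisory support at Health and Wellness Centres, 2.6.3 describes a monthly CHO checklist, and 2.11 describes supervision led by CHOs.

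One secondary objective is "To assess the feasibility of C-COMPASS delivery within the existing ASHA system", measured by 72 h coverage. Another is the incremental cost per woman counselled.

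For cost, section 2.9 says "An incremental cost analysis will be conducted from the health system perspective". It announces three components. Besides training, the programme-level component covers "CHO supervision time, nurse/ANM time for activities and any additional printing or documentation costs". Table 2 has a single supervision row, for CHO time.

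The Discussion states "The marginal resource requirement is a half-day training, a Hindi job aid, and a column in the existing ASHA register", and section 3.1 says that embedding the study in a running programme "ensures that implementation metrics reflect genuine health system performance rather than research-assisted delivery".

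**The concern.** Section 2.6.1 attaches research staff to the delivery of the intervention, whereas section 3.1 says that the metrics do not reflect research-assisted delivery. As written, the two statements do not fit together, and the limitations paragraph does not mention the support.

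The conflict bears on two stated secondary objectives. If study supervisors prompt, accompany or otherwise help ASHAs, the coverage observed is that of the existing system plus an input that would be absent at scale-up. If their time is left out of the costing, the cost per woman leaves out part of what produced that coverage. Both errors point the same way, towards higher coverage and lower cost.

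The Discussion and section 3.2 use these two outputs, at least 70% coverage and a cost set against an INR 200–500 benchmark, in the argument for state and national adoption.

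**Working it through.** **1. The passages side by side**

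| Question | Where | What it says |
|---|---|---|
| Who supports delivery? | 2.6.1 | Study-team supervisors |
| Who supervises? | Introduction, 2.5.2, 2.6.3, 2.11 | HWCs, CHOs, ANMs; study-team supervisors not mentioned |
| Who trains ASHAs? | 2.6.4 | CHOs |
| What is coverage measured from? | 2.8.3 | ASHA registers and CHO supervision records |
| Are the metrics research-assisted? | 3.1 | No |
| Which supervision is costed in the text? | 2.9 | CHO supervision time; nurse/ANM time is listed as well |
| Which supervision is costed in the table? | Table 2 | CHO supervision time only; no nurse/ANM row |

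Study-team supervisors are therefore named in the section on delivery, are absent from the operational sections and from both cost lists, and are in effect denied in 3.1.

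**2. What follows**

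- If the supervisors do nothing towards delivery, 3.1 and the costing can stand and the phrase in 2.6.1 is wrong.
- If they do assist delivery, 3.1 is wrong as worded and the costing omits an input.

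Under neither reading are all the passages right.

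**3. How sensitive the two outputs are**

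No stated figure is in dispute, and the article gives no supervisor time or pay. The arithmetic below shows how much room there is. It does not estimate a bias.

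Expected women in the intervention arm: section 2.12 gives 9.2 per arm per month over 26 weeks. 26 × 7 / 30.44 = 5.98 months, and 9.2 × 5.98 = 55.0, close to the stated 56. I use 56.

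*Coverage (threshold of at least 70%, Discussion).* 0.70 × 56 = 39.2, so 40 timely first contacts are needed.
- 40/56 = 71.4%, which meets the threshold.
- 39/56 = 69.6%, which does not.

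In a result exactly at the margin, one contact that depended on study support decides the outcome. In a result well above the margin, it would not.

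*Cost (INR 200–500 per beneficiary, Discussion).*
- Lower end: 200 × 56 = INR 11,200 in total; 11,200 / 5.98 ≈ INR 1,870 per month for both blocks.
- Upper end: 500 × 56 = INR 28,000 in total; 28,000 / 5.98 ≈ INR 4,680 per month for both blocks.
- Each INR 1,000 per month of supervisor time spent on delivery adds 1,000 × 5.98 / 56 ≈ INR 107 per woman.
- Over an assumed range of INR 2,000 to 20,000 per month, the addition is about INR 214 to 2,136 per woman.

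That range is an assumption with no source in the article. Only the benchmark totals and the cost per INR 1,000 follow from its figures.

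**The case against.** The strongest reply is that one undefined clause is being read as an operating design. The sections that describe how the work is done name health-system staff. The first-contact pathway in 2.6.3 runs from facility notification to the ASHA, with the ANM or facility nurse as back-up, and no study-team step. The clause may simply be loose wording. Supplementary Tables S1 and S2, which are not shown, may describe the roles further. This stands as far as size is concerned: nothing in the article shows that study staff affect any contact. It does not remove the conflict between 2.6.1 and 3.1, which are both current text.

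A second reply is that a health-system perspective properly leaves out research costs. That holds for consent, data collection and outcome assessment. It does not cover time spent helping to deliver the intervention, and 2.6.1 ties the support to delivery.

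A third is that these are secondary aims in a Hybrid Type I study. That is correct, and it limits the weight of the point.

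A reader might infer more: that coverage and cost are biased in fact, that the two objectives cannot be answered, or that supervision is reserved exclusively for CHOs and ANMs. The article supports none of these. The supervisors' role and intensity are undescribed, and 2.5.2 assigns supervision to CHOs and ANMs without excluding others.

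**Conclusion.** The inconsistency is real and should be resolved, in conditional form. To the extent that study-team supervisors assist delivery, 72 h coverage and cost per woman counselled would not describe the existing ASHA system, and both would tend to favour adoption. The direction assumes that support can only help contacts happen and that its omission can only lower the reported cost.

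The size cannot be stated, because the article gives no role, time or pay. What can be said is that a borderline coverage result turns on a single contact, and that supervisor time of about INR 4,680 per month across both blocks would alone equal the upper cost benchmark.

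A reader might also conclude that the 70% threshold should be judged only on contacts made without study support. That does not follow. It would count every supported contact as a failure, including those that would have happened anyway, and so replace a possible upward bias with a downward one.

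The primary EPDS outcome and its sample size are not affected.

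**What to change.** Reconcile 2.6.1 with 2.5.2, 2.6.3, 2.9, 2.11, Table 2 and 3.1 before implementation starts. There are two acceptable routes.

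**Route A: no study support for delivery.** Confine study staff to consent, data collection and outcome assessment, and delete the phrase on study-team supervisors from 2.6.1.

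**Route B: keep the support and make it visible.**
- State what the supervisors do.
- Log each prompt or accompaniment by a study supervisor against the contact concerned.
- Report 72 h coverage overall and for contacts made without such support. Do not treat supported contacts as failures for the 70% threshold.
- Add a row to Table 2 for study-supervisor time spent on delivery support, and report cost per woman with and without it.
- Qualify the statement in 3.1 that the metrics do not reflect research-assisted delivery.

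Route A costs a wording change and the discipline to keep to it. Route B costs one log field and one costing row, and the reported coverage may look lower or the cost higher. Under Route B the log has to run from the first contact: the costing tool in 2.9 is administered at the end of the study, and recall at that stage is a poor substitute for a record made at each contact.

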#### C-COMPASS comprises four structured contacts across the 42-day postpartum period

2.6.2

Table 2.

**Table 2 T2:** Incremental cost analysis- components, data sources, and collection methods.

Cost component	Unit	Data source	Method of estimation
ASHA time: Contact 1 (≤72 h)	Minutes per case	ASHA self-report (end of study)	Time × imputed hourly rate
ASHA time: Day 7 call	Minutes per case	ASHA self-report	As above
ASHA time: Visit 2 (Day 14)	Minutes per case	ASHA self-report	As above
ASHA time: Visit 3 (Day 21)	Minutes per case	ASHA self-report	As above
ASHA time: Contact at 42 days	Minutes per case	ASHA self-report	As above
ASHA transport cost	INR per case	ASHA self-report	Direct expenditure
Printed materials/IEC	INR per case	Programme records	Procurement records
ASHA training (amortised)	INR per case	District records	Total training cost ÷ 3 yrs ÷ annual cases
CHO supervision time	INR per case	CHO self-report	Time×CHO salary rate
Routine care cost (control arm)	INR per case	Control block CHO records	Existing per-woman postnatal expenditure

**Table 3 T3:** Detailed framework selection processes.

SELECT-IT purpose	TMF selected	TMF not selected	Key attribute rationale	Practical consideration
Guiding identification of determinants (barriers/facilitators)	TDF (Theoretical Domains Framework)	CFIR (Consolidated Framework for Implementation Research)	TDF focuses on individual-level behaviour change, aligning with ASHA delivery processes; however, it does not fully capture system-level barriers. Both frameworks are evidence-based.	The study team has qualitative and implementation science expertise and can be using this TDF.
Guiding design and adaptation of strategies	ERIC Taxonomy (Expert Recommendations for Implementing Change)	Implementation Mapping	ERIC provides 73 clearly defined, operationalised strategies with standardised labels and action verbs, enabling direct application in ASHA training and CHO supervision. It has strong alignment with behaviour change evidence. Implementation Mapping was considered more resource intensive.	ERIC tools are readily available and usable without extensive training. Strategies can be directly linked to determinants identified during co-design.
Guiding evaluation and causal explanation	Proctor et al. (13) taxonomy	RE-AIM framework	Proctor's taxonomy includes eight implementation outcomes (acceptability to sustainability) suitable for early-stage evaluations where effectiveness is not yet established. RE-AIM assumes prior evidence on effectiveness and dissemination readiness.	Proctor measures are well-established and align with existing data collection tools, including ASHA feasibility and evaluation matrices.
Guiding the implementation process (study design)	Curran et al. (21) Hybrid Type I	Hybrid Type II or III	Hybrid Type I prioritises effectiveness while concurrently assessing implementation, appropriate for first-time evaluation. Hybrid II/III designs assume greater emphasis on implementation, which is not suitable at this stage.	The design aligns with the Difference-in-Differences analytical approach and is widely recognised as appropriate for early implementation studies.

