Palwal is a predominantly rural district located approximately 80 kilometres south of New Delhi, with a total population of 1,289,685 (HMIS data). The district comprises six health blocks. The district has a sex ratio of 943 females per 1,000 males and a sex ratio at birth of 884 per 1,000 males. The female literacy rate is 68.3% among women aged 15–49 years, with 39.4% having completed 10 or more years of schooling (NFHS-5). The pregnancy rate is 116 per 1,000 women of reproductive age. The HMIS-reported stillbirth rate is 9.4 per 1,000 live births (266 stillbirths among 28,126 live births); however, this substantially underestimates the true burden. SHRiSTI's ASHA-based community surveillance documents a stillbirth rate of 17.2 per 1,000 total births. The perinatal mortality rate reported in HMIS is 14.9 per 1,000 live births which as per the SHRiSTI's ASHA-based community surveillance is around 29.2 per 1,000 live births.

The district health system comprises 1,019 ASHA workers, one District Hospital, one Sub-District Hospital, six Community Health Centres, 14 Primary Health Centres, three Urban PHCs, and 96 Health and Wellness Centres/Sub-centres (92 rural and four urban). Within SHRiSTI, a community-based stillbirth surveillance system has been established in collaboration with district health authorities, with all ASHAs actively reporting across all blocks of Palwal district.

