### Sample size

2.12

Enrolment estimates are derived from SHRiSTI ASHA pregnancy surveillance data which indicates a mean of 4.6 stillbirths per block per month (range: 3.4–5.6), with a seasonal peak during July–October (5.2–5.6 per block per month) *(surveyed data from SHRiSTI project)*. This pattern is consistent with published systematic review by Lakhoo et al. on heat-associated stillbirth risk in South Asian settings in 2025. As described in Section 2.1, the SHRiSTI community-based surveillance estimate of 17.2 per 1,000 total births is used for planning, as it more accurately captures the true community-level burden than the HMIS facility-based figure.. The per-block estimate from the same surveillance data is 4.6 per month and this was used as a base for sample size. The study will employ a difference-in-differences (DiD) design across four blocks (two intervention, two control). With two blocks per arm, the expected enrolment rate is approximately 9.2 women per arm per month. Over the 8-week pre-intervention period, approximately 17 women per arm are expected, and over the 26-week post-intervention period, approximately 56 women per arm are expected, yielding a total sample of approximately 146 women.

The primary outcome is mean EPDS score (continuous). Assuming a clinically meaningful difference of 3.5 points, a pooled standard deviation of 6.5, two-sided alpha of 0.05, and 80% power, a minimum of 55 women per arm in the post-intervention period is required. The expected sample size of 56 per arm provides approximately 81% power. To account for an anticipated 10% attrition rate, the post-intervention data collection period may be extended to ensure a minimum effective sample size of 56 women per arm.

A pre-specified sensitivity analysis including early neonatal deaths (<24 h) is expected to add approximately 18 cases per arm. This estimate is based on a neonatal mortality rate of ∼22 per 1,000 live births in Haryana, with approximately 25% of deaths occurring within 24 h, applied to an estimated 277 live births per block per month. This yields approximately 1.5 early neonatal deaths per block per month, resulting in ∼18 additional cases per arm over the study period. The resulting post-intervention sample of approximately 74 per arm would provide approximately 91% power.

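### Training cost rests on one undiscounted three-year life that the study cannot test, and over a range of training costs that choice alone decides whether training stays under ₹500 per woman

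*Protocol article*

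**What the plan says.** Table 2 (section 2.6.2) gives the training component as "Total training cost ÷ 3 yrs ÷ annual cases". Section 2.9 agrees: training costs are "amortised over three years and allocated per expected annual caseload". The same section reports costs in 2026 rupees and says "no discounting will be applied given the short study duration". Its primary metric is the incremental cost per woman counselled. The article gives no reason for three years and names no other period.

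The Discussion says the cost analysis will determine whether C-COMPASS "falls within the ₹200–500 per beneficiary threshold typical of scalable LMIC community health programmes". Section 2.9 speaks more loosely of interpreting findings against existing benchmarks.

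The figures that determine how many women share the training cost are elsewhere. Section 2.1 states "The district health system comprises 1,019 ASHA workers" and six health blocks. Section 2.12 plans on "a mean of 4.6 stillbirths per block per month". Section 3.1 gives a second ASHA count: "surveillance data from 895 ASHAs across all Palwal blocks".

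**The concern.** Dividing by three treats one round of training as useful for three years. The post-intervention period is about 26 weeks, so the study cannot show whether that is so. The reason given for not discounting refers to the length of the study, while the cost is spread over a horizon several times longer.

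This would matter little if each trained ASHA saw many cases. Here many ASHAs are trained for few stillbirths, so training may be a large part of the cost per woman, and the assumed life scales that part directly. The result is then read against a numerical threshold meant to inform programme adoption.

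**Working it through.** **Inputs from the article.** 1,019 ASHAs (or 895) in six blocks; two intervention blocks; 4.6 stillbirths per block per month; 1.5 early neonatal deaths per block per month (section 2.12); 28,126 live births and 17.2 stillbirths per 1,000 total births in the district (section 2.1).

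**Assumptions.** ASHAs and births are spread evenly over the six blocks, because block counts are not given. C, the cost of training one ASHA in rupees, is not stated and is left free.

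**The plan's own caseload.** 4.6 × 2 = 9.2 women per arm per month, as stated. Over 8 weeks, 9.2 × (12/52) × 8 = 17.0 (stated 17). Over 26 weeks, 9.2 × 6 = 55.2 (stated 56). Total 2 × (17 + 56) = 146, as stated. The planning rate reproduces.

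**ASHAs trained.** 1,019/6 × 2 ≈ 340.

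**Women per year in two blocks, on three readings of the article.**
- Stillbirths at the planning rate: 4.6 × 2 × 12 = 110.4.
- With early neonatal deaths: (4.6 + 1.5) × 2 × 12 = 146.4. (That this resembles the total sample of 146 is coincidence.)
- From the district rate: 28,126 × 0.0172/(1 − 0.0172) ≈ 492 in the district; 492 × 2/6 = 164.

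At 110.4 cases, one stillbirth falls to each ASHA every 340/110.4 ≈ 3.1 years. On the other two caseloads it is one woman every 2.3 or 2.1 years.

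**Training cost per woman** = C × ASHAs trained/(life in years × women per year). The crossing range is the set of C for which training alone is at or below ₹500 over three years and above ₹500 over one year: from 500/(one-year multiple) to 500/(three-year multiple).

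| Women per year | 3-year life | 2-year life | 1-year life | Crossing range of C |
|---|---|---|---|---|
| 110 | 1.03 × C | 1.54 × C | 3.08 × C | ₹163–488 |
| 146 | 0.77 × C | 1.16 × C | 2.32 × C | ₹216–647 |
| 164 | 0.69 × C | 1.04 × C | 2.07 × C | ₹241–724 |

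With 895 ASHAs (about 298 trained) and 110 women a year, the multiples are 0.90 and 2.70 and the range is ₹185–555.

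**Illustration at C = ₹200 (assumed).** Over three years: ₹205, ₹155 and ₹138 for the three caseloads. Over one year: ₹615, ₹464 and ₹414. At this C, only the lowest caseload takes training past ₹500.

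**Discounting.** Annualising over three years multiplies the charge by 3/(sum of discount factors). At 3% this is 1.03 (payments at the start of each year) to 1.06 (at the end); at 5% it is 1.05 to 1.10.

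**The case against.** The three-year life is openly stated, consistent between Table 2 and section 2.9, and arithmetically sound. Nothing in the article supports one year over three. The cost per ASHA trained is not given, so any rupee figure depends on an assumed input, and the wider caseloads soften the result. Discounting is a small matter. The ₹200–500 band appears only in the Discussion, and the article does not say whether the band itself includes amortised training. All of this stands, and it limits the point to a sensitivity analysis.

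A reader might go further in three ways that the documents do not support.
- **That training lapses before it is used.** Sparse cases show only that many ASHAs share few women. On a Poisson assumption at 110 cases a year, about 38% of trained ASHAs would meet no stillbirth in three years, but that says nothing about how long skills last. A job aid, supportive supervision and monthly CHO checks are described, and CHO supervision is costed separately.
- **That refreshers or alternative periods are ruled out.** The article is silent on them, and a condensed article may leave both to the full plan.
- **That the three-year divisor decides whether the band is met.** It does so only for C within the ranges above.

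What the objection does not remove is that one unsupported life carries a stated threshold comparison, and that the reason given for not discounting does not match the horizon.

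**Conclusion.** The point holds as a minor, inexpensive improvement to a stated method. Three years is not an error. It is a single assumption that this study cannot test, and moving from three years to one triples the training component whatever C is. Whether that takes training alone past ₹500 depends on C: it does for about ₹163–488, ₹216–647 or ₹241–724 at 110, 146 or 164 women a year. Below each range training alone stays under the ceiling at both lives; above it, training alone exceeds the ceiling at both. Other cost components come on top, so the ranges for the total would start and end lower.

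The missing discount rate is mainly a fault of reasoning, worth about 3–6% of the training component at a 3% rate. The result rests on an even spread of ASHAs and births over blocks and on the article's planning rates.

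C is also unsettled within the article. Section 2.6.3 describes the training as full-day, while section 2.6.4 and the Discussion call it half-day. These passages need to be reconciled, because training length feeds directly into C.

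**What to change.** Keep the three-year life as the base case and annualise it with a stated discount rate. Report the incremental cost per woman counselled at one-, two- and three-year training lives as a sensitivity analysis, and state which women count in the annual caseload. Say without qualification that C-COMPASS does not exceed ₹500 per woman only if this holds at all three lives; otherwise say that the conclusion depends on the assumed life. Frame the test on the upper limit, so that a cost below ₹200 is not counted as a failure.

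No new data are needed, and the change can be made before costs are collected at the end of the study. The price is a few more lines in the cost table and possibly a less favourable headline figure.
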